## Abstract

**Background:**

Neck pain is a common symptom in most patients suffering from cervical radiculopathy. However, some conservative treatments are limited by their modest effectiveness. On the other hand, surgical intervention for cervical disc disorders is indicated when symptoms are refractory to conservative treatments and neurological symptoms are progressive. Many patients use complementary and alternative medicine, including traditional Chinese medicine, to address their symptoms. The purpose of the present study is to examine the efficacy and safety of Qishe Pill, a compound traditional Chinese herbal medicine, for neck pain in patients with cervical radiculopathy.

**Methods/design:**

A multicenter, double-blind, randomized, placebo-controlled trial to evaluate the efficacy and safety of the Qishe Pill is proposed. The study will include 240 patients from five sites across China and diagnosed with cervical radiculopathy, according to the following inclusion criteria: age 18 to 65 with pain or stiffness in the neck for at least 2 weeks (neck disability index score 25 or more) and accompanying arm pain that radiates distally from the elbow. Qualified participants will be randomly allocated into two groups: Qishe Pill group and placebo group. The prescription of the trial medications (Qishe Pill/placebo) are 3.75 g each twice a day for 28 consecutive days. The primary outcome is pain severity. Secondary outcomes are functional status, patient satisfaction, and adverse events as reported in the trial.

**Discussion:**

Qishe Pill is composed of processed *Radix Astragali*, Muscone, *Szechuan Lovage Rhizome*, *Radix Stephaniae Tetrandrae*, Ovientvine, and *Calculus Bovis Artifactus.* According to modern research and preparation standards, Qishe Pill is developed to improve on the various symptoms of cervical radiculopathy, especially for neck pain. As it has a potential benefit in treating patients with neck pain, we designed a double-blind, prospective, randomized-controlled trial and would like to publish the results and conclusions later. If Qishe Pill can alleviate neck pain without adverse effects, it may be a unique strategy for the treatment of cervical radiculopathy.

**Trial registration:**

This study is registered at ClinicalTrials.gov, NCT01274936

## Background

Cervical radiculopathy is a distinct consideration in the evaluation of any patients who have neck pain and may be defined simply as an abnormality of a nerve root, which originates in the cervical spine [1]. The typical cervical radiculopathy patient presents neck and arm discomfort of insidious onset. The discomfort can range from a dull ache to a severe burning pain. Typically, pain is referred to the medial border of the scapula, and the patient’s chief complaint is shoulder pain. As the radiculopathy progresses, the pain radiates to the upper or lower arm and into the hand, along the sensory distribution of the nerve root that is involved. The initial approach to the management of cervical spondylopathic radiculopathy is nearly the same as that of non-specific neck or back pain that can be found in most patients. Conservative treatments include non-steroidal anti-inflammatory drugs, narcotics, muscle relaxants, physical therapy, and transcutaneous electrical nerve stimulation. The main objectives of conservative treatments are to relieve pain and improve function and health-related quality of life [2]. However, these treatments for cervical radiculopathy are limited by their modest effectiveness [2]. Surgical treatment for cervical disc disease is indicated when symptoms are refractory to conservative treatments and neurological symptoms are progressive [3]. In terms of pharmacotherapy, there is generally no randomized, placebo-controlled trial available comparing standard non-surgical treatment [4]. Therefore, care plans should be designed based principally on accumulated experience, locally available services, and patient preferences. Treatment plans are developed to alleviate pain, improve function, and prevent recurrence [2].

As a complementary and alternative medicine, herbal medicines have the potential to avoid the adverse effects of medications and surgery [4]. Natural substances, including herbal medicines, have been used to promote healing and alleviate neck pain in western countries [5]. Previous studies have demonstrated that some active substances in herbal medicine can promote Qi flow and blood circulation to alleviate pain.

A number of studies on the effects of the Chinese herbal medicine on cervical radiculopathy have been proposed, but useful empirical research is insufficient. For chronic neck pain, with or without radicular symptoms, there is low quality evidence suggesting that herbal medicine is more effective than placebo for pain relief as measured at the end of the treatment [6]. Moreover, the size of the studies has been small and the effect was measured only in the short-term. Further research is very likely to change both the effect size and our confidence in the results. There is a need for randomized-controlled trials (RCTs) with adequate numbers of participants that address long-term efficacy of herbal medicines compared to placebo.

Using a well-designed clinical trial, we will survey the efficacy of concurrent use of this remedy in relieving neck pain. Therefore, the present study is designed to examine efficacy and safety of Qishe Pill, a traditional Chinese herbal medicine (TCM) compound, on neck pain in cervical spondylopathic radiculopathy in a randomized, double-blind, placebo-controlled trial. Results of this study will provide evidence regarding the value of Qishe Pill as an intervention to alleviate neck pain caused by cervical radiculopathy.

### Details of intervention

Qishe Pill is composed of processed *Radix Astragali*, Muscone*, Szechuan Lovage Rhizome*, *Radix Stephaniae Tetrandrae*, Ovientvine*,* and *Calculus Bovis Artifactus* (Table 1) [7].

**Table 1 T1:** Standard formula (Capsule ingredients)*

**Chinese name**	**Pharmaceutical name**	**Powered herb,%**
Huang Qi	*Radix Astragali*	28%(13 g)
She Xiang	Muscone	0.06%(0.03 g)
Chuan Xiong	*Szechuan Lovage Rhizome*	26%(12 g)
Fang Ji	*Radix Stephaniae Tetrandrae*	19%(9 g)
Qing Feng Teng	Ovientvine	26%(12 g)
Niu Huang	*Calculus Bovis Artifactus*	0.6%(0.3 g)

*Pharmaceutical Terminology from Hsu [7].

Qishe Pill is a thin 0.15 g film-coated pill; removal of the film reveals alight brown to brown colour. The pill has a slight odor and tastes bitter. The dosage is 25 pills, twice daily, with a total daily dosage of 7.5 g, which is in the dosage range defined by the National Center for Complementary and Alternative Medicine: *Astragalus mongholicus* 9–30 g; *Rhizoma ligustici wallichii* 3–9 g; *Radix Stephaniae Tetrandrae* 4.5–9 g; *Caulis Sinomenii* 6–12 g; Muscone 0.03–0.1 g; *Calculus Bovis Artifactus* 0.15– 0.35 g.

The production process of Qishe Pill: (1) Volatile oil is extracted from *Rhizoma ligustici wallichii*. (2) The remaining drugs forma decoction is mixed with *astragalus membranaceus* soaked for 30 minutes and simmered in 10 times the amount of water, twice, for 2 hours each time. (3) The decoction is then vacuum filtrated to a concentration of relative density 1.24-1.26 (70°C). Ethanol is mixed into the concentrated decoction to reach 70% alcohol content. (4) After standing, filtering, and concentrating with recovery of ethanol, the decoction is crushed into a fine powder after vacuum drying. (5) In the reagent of 14 times the amount of 70% ethanol, *Radix Stephaniae Tetrandrae* and *Caulis Sinomenii*are is extracted with the circumfluent alcohol three times, once 2 hour. (6) Volatile oil of *Rhizoma ligustici wallichii* is mixed with 4 times the amount of β-cyclodextrin and then dried in vacuum. (7) The porphyrization of *Artificial Calculus Bovis Artifactus* and *Artificial Muscone* is mixed with β-cyclodextrin and other accessories to be made into a piece, pelleted and coated pills. These pills are called Qishe Pill in drug name.

The placebo is composed of β-cyclodextrin, colorants and food flavoring, to look and taste similar to Qishe Pill.

## Methods/design

### Study design

This clinical trial is a multi-center, randomized, double-blind, placebo-controlled design. Participants will be enrolled by clinic recruitment at five hospital sites (Longhua Hospital, Shanghai University of TCM; Huadong Hospital, Fudan University; Affiliated Hospital of Changchun University of TCM; TCM Hospital of Gansu province; and TCM Hospital of Suzhou city). Participants will be recruited in equal numbers (n=48) from each of the five sites.

### Ethical issues

This study has been approved by the Institutional Review Board of Longhua Hospital, Shanghai University of TCM on November 30^th^ 2011 (No: 2011LCSY031). All study participants will sign the written informed consent prior to participation. All patients will receive written and oral reassurance regarding the typical benign course of the symptoms. We will explain that placebo and treatment with Qishe Pill might be equally effective interventions. Patients in all treatment groups will be allowed to use painkillers when necessary. In general, paracetamol is selected with or without a non-steroidal anti-inflammatory drug. Patients will be asked to note their drug use, including over-the-counter analgesics, in a specially designed diary during the first four weeks following randomization.

### Patient population and recruitment procedure

All participants will be selected from the general outpatient clinic offive hospital sites, where the patients willbe diagnosed with cervical radiculopathy confirmed by a neurologist, and then diagnosed based upon clinical manifestations (pain along the cutaneous distribution of one or more cervical roots, which may include weakness and hyporeflexia), physical examination, and imaging [4].

Inclusion criteria are age between 18 and 65 years, pain or stiffness in the neck for at least 2 weeks, neck symptoms reproducible during physical examination, neck pain on neck disability index (NDI) of 18 or more, and radiation of arm pain distal to the elbow, plus at least one of provocation of neck or arm pain by neck movements, Brachial plexus traction test, foraminal compression test, or foraminal separation test, sensory changes in one or more adjacent dermatomes, or muscle weakness in one or more adjacent myotomes. Further inclusion prerequisites are willingness for treatment and to adhere to measurement regimens, no involvement in litigation, and written informed consent.

Excluded criteria are patients whose history, signs, and symptoms suggested a potential non-benign cause (including previous neck surgery) or evidence of a specific pathologic condition, such as malignancy, neurologic disease, fracture, herniated disc, or systemic rheumatic disease, clinical signs of spinal cord compression, previous neck trauma or treatment with surgery, obvious vertigo, pregnant women, lactating women, currently participating in other clinical trials, accompanied with hepatic, renal, hematopoietic system, endocrine system, cardiovascular, nervous system, primary and other serious diseases (serum ALT, AST, ALP, TBIL, DBIL, Cr or BUN more than two-fold than the upper limit of reference value), tuberculosis, vertebral deformities, cancer and mental illness, and insufficient understanding of the Chinese language, and/or have been treated with physical therapy or manual therapy for neck pain during the previous 2 weeks.

Patients with concurrent headaches, non-radicular pain in the upper extremities, and low back pain will not be excluded, but neck pain has to be the main symptom for all patients [8].

Patients will be recruited from May 2012 to Oct 2013 from the five sites in China. The review board at each institution approved the protocol. The study is organized and coordinated by Longhua Hospital, Shanghai University of TCM in Shanghai, China.

This study is to be conducted according to the protection of patients, as outlined in the Declaration of Helsinki, and approved by the appropriate Institutional Review Boards. Each participant will sign the written informed consent before undergoing any examination or study procedure, in compliance with Good Clinical Practice. Patients who initially meet these eligibility criteria are then to complete the additional baseline testing and will be randomized into either the treatment or the control group. An independent steering committee will oversee the study.

### Interventions

At randomization, patients will be assigned to receive Qishe Pill (or matching placebo) at 3.75 g twice per day. In this study, the same outer packing will be used for both Qishe Pill and the matching placebo. Therefore, the treating physicians, participants and investigators will be blinded to treatment assignment. The Qishe Pill and matching placebo used in the trial are both manufactured and provided by a pharmaceutical company that meets the requirements of Good Manufacturing Practice. All significant medicine information, including ingredient composition, heavy metals, etc., is provided by the same company.

Follow-up visits will be continued for 5 months. At each visit, data will be collected on the outcome events, compliance and adverse reactions leading to a discontinuation of study medications. All primary and secondary events will be documented and be centrally adjudicated with the use of standardized definitions.

### Randomization and allocation

Treatment allocation occurs when the study participant meets the inclusion criteria and signs the informed consent form. All participating patients will be randomized using a computerized block randomization schedule with a multiple block size of four; 240 patients will be randomly generated and kept in sequentially numbered opaque envelopes. All of the Qishe Pill and placebo provided by the pharmaceutical company will be numbered with a label according to the randomization schedule. When researchers administer the intervention medicine (Qishe Pill or matching placebo), these should be administered according to the randomized number. Randomization and uncovering must be conducted by a statistician team as a third party. As a result, researchers and patients are totally blinded to treatment allocation; the only un-blinded individual is the statistician responsible for the randomization process. The treatment assignments are balanced within each block.

### Outcome measurements

The primary study outcome is pain severity (measured with a visual analogue scale (VAS)). Secondary outcomes are a composite of functional status (measured by NDI), patient satisfaction, and adverse events as reported in the trial. The VAS measures the amount of pain, which is a pain score ranging from 0 (no pain) to 100 mm (very severe pain) [9]. Operationally, the VAS score is displayed as a horizontal line, 100 mm in length, with word descriptors anchored at each end. The patient marks on the line the point that they feel represents their perception of their current pain. The VAS score is then determined by measuring in millimeters from the left hand end of the line to the point that the patient marks. The VAS score and NDI will be measured at all the measurement points (baseline, 2 and 4 weeks of treatment duration, and 2 and 5 months of follow-up duration).

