### Study schedule

The measurements that need to be performed at each visit are listed in Table 2.

**Table 2 T2:** Study schedule of clinical trial (6 months)

	**Initial screening**		**Treatment times**		**Follow-up**	
	**Visit 1**	**Visit 2**	**Visit 3**	**Visit 4**	**Visit 5**	**Visit 6**
	**Week 0**	**Week 1**	**Week 2**	**Week 4**	**Month 2**	**Month 5**
Determined the exclusion criteria	Yes					
Informed consent	Yes					
Randomized	Yes					
Weight	Yes		Yes	Yes		
Blood pressure	Yes		Yes	Yes		
Heart rate/Rhythm	Yes		Yes	Yes		
Respiratory rate	Yes		Yes	Yes		
Spurling’s test	Yes					
Brachial plexus force test	Yes					
Drug allergy history	Yes					
Blood routine	Yes			Yes		
Urine routine	Yes			Yes		
Excrement routine	Yes			Yes		
Occult blood	Yes			Yes		
ECG	Yes			Yes		
Liver function test	Yes			Yes		
Kidney function test	Yes			Yes		
X-ray (frontal and lateral)	Yes			Yes		
Concomitant medication		Yes	Yes	Yes		
VAS scores	Yes	Yes	Yes	Yes	Yes	Yes
NDI scores	Yes		Yes	Yes	Yes	Yes
SF-36 scores		Yes	Yes	Yes		
The medicine issue		Yes	Yes			
Compliance assessment			Yes	Yes		
Degree of satisfaction				Yes		
Safety evaluation		Yes		Yes		

ECG: Electrocardiogram; VAS: Visual analogue scale; NDI: Neck disability index: SF-36: The MOS item short from health survey.

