### Sample size considerations

We calculated the sample size for this two arm trial on the basis of the comparison treatment (Qishe Pill) versus placebo, with equal allocation in the treatment arms and five repeated measurements (at entry, at 2 and 4 weeks’ treatment, and at 2 and 5 months’ follow-up), with an estimated correlation coefficient of the measurements of ρ=0.8 and a difference in the mean value of the VAS for neck pain of 12 mm, as a clinical relevant difference with an estimated standard deviation in each treatment group of 25 mm [10]. As neck pain is the main complaint in cervical radiculopathy, we chose this outcome to calculate the sample size. Under the setting of alpha = 0.05 and power = 90%, the calculated sample size of each group is around 96. Considering 20% loss to follow-up, the total sample size needed to detect this difference at a 5% level of significance with a power of 90% is 240 patients.

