### Statistical analysis

The data will be collected and analyzed according to the intention-to-treat principle. Standard statistical techniques will be used to describe characteristics of patients in both groups. We will compare baseline characteristics in both groups and if incomparability appears, we will perform the secondary analysis, adjusting for differences. The primary outcome, amount of pain, will be compared between both groups using survival analysis and analysis of variance for repeated measures. If adjustment for possible baseline incomparability is needed, analysis of covariance will be performed. We will use multivariate analysis to do retrospective analysis with the baseline data of the effective cases and ineffective cases in the treatment group. Differences in the baseline data will be used to optimize the inclusion criteria. We will do subgroup analysis based on severity of pain (VAS=70 mm) and use of analgesics.

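### The primary VAS has five measurement points in the text but six in Table 2, and the article does not say which readings enter the repeated-measures comparison or whether the extra one (Week 1) precedes treatment

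*Protocol article*

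**What the plan says.** Four places in the protocol article bear on this.

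- **Outcome measurements.** The schedule for both scales is given as "The VAS score and NDI will be measured at all the measurement points (baseline, 2 and 4 weeks of treatment duration, and 2 and 5". That makes five points, the last two in months of follow-up, with no Week 1.
- **Sample size considerations.** The calculation uses "five repeated measurements (at entry, at 2 and 4 weeks’ treatment, and at 2 and 5 months’ follow-up", the same five.
- **Study schedule, Table 2.** The VAS row reads "VAS scores Yes Yes Yes Yes Yes Yes", one tick for each of the six visits, including Visit 2 at Week 1. The NDI row reads "NDI scores Yes Yes Yes Yes Yes": five ticks, with Visit 2 blank, which agrees with the text.
- **Statistical analysis.** The primary outcome "will be compared between both groups using survival analysis and analysis of variance for repeated measures". The readings that enter are not named. Analysis of covariance is foreseen only if the groups turn out not to be comparable at baseline.

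On timing, Table 2 places randomization at Visit 1 (Week 0), but its supply row, "The medicine issue Yes Yes", has its ticks at Visits 2 and 3 (Weeks 1 and 2).

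**The concern.** The mismatch affects the primary outcome alone. Because the NDI row agrees with the text, a general shift in visit numbering or a damaged table does not explain it.

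It matters because the group effect in a repeated-measures analysis of variance is the average difference over the readings entered. A reading taken before treatment has no expected difference and pulls that average down. A reading taken on treatment may carry part or all of the effect. What the sixth reading does therefore depends on two things the article leaves open: whether it is analysed, and which side of the first dose it falls on.

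**Working it through.** **Inputs.** From Sample size considerations: difference 12 mm, SD 25 mm, correlation 0.8, 96 per group before loss, 20% loss, 240 in total. Error rates: "Under the setting of alpha = 0.05 and power = 90"%. Assumptions of this check: two-sided test, compound symmetry, no difference at baseline, and 12 mm at each of Week 2, Week 4, Month 2 and Month 5. The article gives only the single figure of 12 mm, so the profile over time is assumed.

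**The plan's own figure.** A simple two-group comparison needs 2 × (25 × (1.960 + 1.282) / 12)² = 91.2, so 92 per group. With the mean of five readings the variance factor is (1 + 4 × 0.8)/5 = 0.84, and 91.2 × 0.84 = 76.6, so 77. Neither gives 96. The step from 96 to 240 does reproduce: 96/0.8 = 120 per group. How 96 arose is a separate matter. It is used here as the number analysed.

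**Group main effect with k readings.** The effect is the mean of the k differences. SD of a patient's mean = 25 × √((1 + (k − 1) × 0.8)/k). SE = SD × √(2/n). Power ≈ Φ(effect/SE − 1.96).

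- k = 5: SD = 25 × √0.84 = 22.91; SE at 96 = 3.31.
- k = 6: SD = 25 × √0.833 = 22.82; SE at 96 = 3.29.

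| Readings entered | Mean effect | Power, 96 per group | Power, 120 per group |
|---|---|---|---|
| Five: 0, 12, 12, 12, 12 | 48/5 = 9.6 mm | 82.7% | 90.1% |
| Six, Week 1 = 0 mm | 48/6 = 8.0 mm | 68.0% | 77.5% |
| Six, Week 1 = 6 mm | 54/6 = 9.0 mm | 78.0% | 86.3% |
| Six, Week 1 = 12 mm | 60/6 = 10.0 mm | 85.9% | 92.4% |

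**Break-even.** Six readings match five when (48 + d)/6 = 9.6 × 22.82/22.91 = 9.56, so d ≈ 9.4 mm. Below that the sixth reading costs power; above it there is a slight gain.

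**Group-by-time test.** Noncentrality = (n/2) × Σ(d − mean d)² / (625 × 0.2). At 96 per group this is 48 × 115.2/125 = 44.2 with five readings and 48 × 192/125 = 73.7 with six and Week 1 at zero. Power is above 99.9% in every case in the table.

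**Which side of the first dose is Week 1?** First issue of medicine at Visit 2 points to before treatment. Against that, the text calls the later points 2 and 4 weeks of treatment. These match Weeks 2 and 4 only if treatment starts at Week 0. Counted from Week 1 they would be 1 and 3 weeks. The article supports both readings and settles neither.

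**Four later readings as the outcome.** The effect is the full 12 mm. Variance factor = (1 + 3 × 0.8)/4 = 0.85, SD 23.05, power 95.0% at 96 per group without adjustment. With one baseline value as covariate the factor is 0.85 − 0.64 = 0.21, and the 95% interval half-width is 1.96 × 25 × √(2 × 0.21/96) = 3.2 mm; power exceeds 99.9%.

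**The case against.** The strongest reply is that Table 2 is a collection schedule. A scheduled reading need not be analysed. The only section that sizes the comparison says five, the outcome section agrees, and naming the readings in the model is commonly left to an analysis plan that is not shown. If Visit 2 is before treatment, the six ticks may simply be one screening value plus the five points in the text, leaving only the question of which early value is the baseline. All this is fair. A reader might infer that the trial will analyse six readings and so has only 68% power; the documents do not support that, because no section says that six readings enter the model. A reader might also infer that the set will be picked after the results are seen; nothing in the article suggests it.

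Two further limits stand. The loss concerns the group main effect, which the Statistical analysis section does not single out, and the group-by-time test hardly moves. Also, the five-reading benchmark of 83% is already below the planned 90%, because the baseline is counted as an outcome. That shortfall does not come from the sixth reading.

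It is also tempting to average Week 1 with Week 0 as a two-reading baseline. This is unsafe as a default. Week 1 follows randomization, and if patients are already taking the medicine the adjustment would remove part of the treatment effect.

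What survives is the contradiction itself. The article fixes the number of primary readings at five in two sections and at six in its schedule, and nothing shown reconciles them.

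**Conclusion.** The inconsistency is real, specific to the primary outcome and cheap to correct. Its effect on power is conditional. If Week 1 is before treatment and enters as a repeated outcome, the group effect drops by 1.6 mm (9.6 to 8.0) and power by about 15 percentage points at 96 per group. If Week 1 is on treatment with a 6 to 12 mm difference, power lies about 5 points below to 3 points above the five-reading figure. These results rest on compound symmetry, correlation 0.8, SD 25 mm, a two-sided 5% test and 12 mm at all four later visits. The point should be settled before unblinding. It does not show that the planned analysis is underpowered.

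**What to change.** 1. Make Outcome measurements, Sample size considerations and Table 2 agree on one list of VAS readings.
2. State whether the Visit 2 VAS is taken before the first dose, and reconcile randomization at Week 0 with first issue of medicine at Week 1. Which of these timings is right is for the sponsor to say.
3. In Statistical analysis, define the treatment comparison on Week 2, Week 4, Month 2 and Month 5, with the baseline VAS as a covariate in every case and not as one of the outcomes. This replaces the present rule of adjusting only if the groups look different. Restate the sample-size text for the same comparison.
4. Use the Visit 2 VAS on the baseline side only if it is confirmed to precede the first dose in every patient. Otherwise list it as an on-treatment reading and state, before unblinding, whether it enters the primary comparison.

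The cost is wording in the protocol and analysis plan. No visits, data or patients are added, since Table 2 already schedules the Week 1 VAS. If two early readings do come to form the baseline, a patient missing one would have a baseline resting on the other alone, which is a small drawback.
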